## Abstract

**Background:**

Chronic kidney disease (CKD) is a global public health problem. Currently, as for advanced CKD populations, medication options limited in angiotensin-converting enzyme inhibitors (ACEi) and angiotensin receptor blockers (ARB), which were partially effective. A Chinese herbal compound, *Bupi Yishen* formula, has showed renal protective potential in experiments and retrospective studies. This study will evaluate the efficacy and safety of *Bupi Yishen* formula (BYF) in patients with CKD stage 4.

**Design:**

In this double blind, double dummy, randomized controlled trial (RCT), there will be 554 non-diabetes stage 4 CKD patients from 16 hospitals included and randomized into two groups: Chinese medicine (CM) group or losartan group. All patients will receive basic conventional therapy. Patients in CM group will be treated with BYF daily while patients in control group will receive losartan 100 mg daily for one year. The primary outcome is the change in estimated glomerular filtration rate (eGFR) over 12 months. Secondary outcomes include the incidence of endpoint events, liver and kidney function, urinary protein creatinine ratio, cardiovascular function and quality of life.

**Discussion:**

This study will be the first multi-center, double blind RCT to assess whether BYF, compared with losartan, will have beneficial effects on eGFR for non-diabetes stage 4 CKD patients. The results will help to provide evidence-based recommendations for clinicians.

**Trial registration:**

Chinese Clinical Trial Registry Number: ChiCTR-TRC-10001518.

## Background

The high incidence of chronic kidney disease (CKD) and associated poor outcomes presents a major public health problem in many developed countries. The prevalence of CKD ranges from 9.4 to 13.0 % in China [1, 2], which is similar to the reported prevalence in North America [3, 4] and Australia [5].

Patients with CKD are at a high risk of cardiovascular events and can gradually develop end stage renal disease (ESRD), with a decreasing estimated glomerular filtration rate (eGFR) of 2 to 20 ml/min/1.73 m^2^ per year [6]. Patients with ESRD require renal replacement therapy to maintain their life, and the rising prevalence of CKD represents an increasing economic burden to many countries. For example, in Taiwan, only 7.7 % of those over the age of 65 are diagnosed with CKD, but 15.9 % of the national health care expenditure is spent treating this condition [7].

The current treatments applied to delay the progression of CKD are limited and only partially effective. Angiotensin-converting enzyme inhibitors (ACEi) and angiotensin receptor blockers (ARBs) are recommended for their antihypertensive and proteinuria-reducing effects [5]. However, ACEi or ARBs can only reduce the risk of ESRD by 50 % [8]. The risks of adverse events including hyperkalemia and acute kidney injury limit the application of ACEi/ARBs in advanced CKD (stages 4 and 5) and elderly patients [9]. Aside from ACEi/ARB and complication management, there are no effective treatments for advanced CKD [5]. Thus, a novel, economical and effective intervention is urgently sought.

In China, Chinese medicine (CM) is widely applied for CKD and an evidence-base application of CM is gradually accumulating. Several large clinical studies have indicated benefit effects of Chinese herbal medicine in early stage CKD patients [10, 11]. However, CM interventions for stage 4 CKD populations are lacking, and further investigations are required to evaluate the risks and benefits of CM in this subgroup population.

*Bupi Yishen* formula (BYF), a Chinese herbal compound, was developed from the classical Chinese prescription Sijunzi decoction, and was modified according to data mining 10,000 CKD stage 4 outpatient records. BYF exhibited a potential renal protective effect in preliminary unpublished observational studies. Twenty-six CKD stage 4 patients were treated with BYF orally once a day based on conventional western therapy. After one-year, eGFR decline was observed in 17 of 26 patients, with a mean reduction of 2.39 (mean: 2.39, standard deviation: 5.59). The decline of eGFR was slower than 6.8 ml/min/1.73 m^2^ per year receiving benazepril in patients with CKD stage 4 that observed in Hou’s study [12].

Components of BYF include *Astragalus mongholicus* (Huangqi), *Codonopsis pilosula* (Dangshen), *Macrocephalae* (Baizhu), *Poria cocos* (Fuling), *Rhizoma dioscoreae* (Shanyao), *Semen coici* (Yiyiren), *Radix polygoni multiflori* (Heshouwu), *Semen cuscutae* (Tusizi), and *Salvia miltiorrhiza* (Danshen). Some of these components have been reported to reduce proteinuria, inhibit renal fibrosis and improve renal function in experimental studies [13–16]. Based on this evidence, a trial was designed to assess the efficacy and safety of BYF for delaying progression in patients with non-diabetes stage 4 CKD. The efficacy of BYF was compared with an Angiotensin II antagonist, Losartan.

## Design and Methods

### Study design

This multi-center, double blind, double dummy, randomized controlled trial (RCT) will be conducted in China (see Fig. 1). Approximately 554 patients will be divided into the CM group or losartan group at a 1:1 ratio.

**Fig. 1 Fig1:**
[figure not shown]
Clinical trial flow diagram

**Fig. 2 Fig2:**
[figure not shown]
Ultra-performance liquid chromatography-mass spectrometry pattern of Bupi Yishen formula

**Fig. 3 Fig3:**
[figure not shown]
Mass spectra of Bupi Yishen formula (ultraviolet; positive ion mode; negative ion mode)

### Ethics approval and registry

The study will be conducted in accordance with the Declaration of Helsinki, and was approved by the Ethics Committee of Guangdong Provincial Hospital of Chinese Medicine (No. B2010-11-03). The study was registered at the Chinese Clinical Trial Registry (No. ChiCTR-TRC-10001518). Written informed consent will be obtained from each eligible patient.

### Settings

The study will be organized by the Guangdong Provincial Hospital of Chinese Medicine and conducted at 16 centers identified as tertiary level TCM hospitals from different provinces in China.

### Participants

All patients diagnosed with stage 4 CKD and CM syndrome-spleen and kidney qi deficiency (SKQD) will be recruited. Stage 4 CKD is defined as a severe reduction in eGFR of 15–29.9 ml/min/1.73 m^2^ for at least 3 months [17]. SKQD is a CM diagnose based on clinical symptoms, signs, tongue appearance and pulse [18, 19], and was confirmed by two senior physicians.

### Inclusion and exclusion criteria

The participant inclusion criteria are as follows: age from 18 to 80 years; diagnosed with stage 4 CKD at least 3 months prior to enrollment; blood pressure below 140/90 mmHg.

The participant exclusion criteria are as follows: imminent initiation of renal replacement therapy; current corticosteroid or immunosuppressive therapy; serious arrhythmia, heart failure (New York Heart Association Functional Classification stage 4), myocardial infarction, unstable angina, or cerebrovascular accident; concomitant diabetes, malignant tumor, hepatitis B, decompensating liver cirrhosis, active tuberculosis, acute infectious disease contributing to CKD progression, or any condition (mental or physical) that would interfere with participants’ ability to comply with the study protocol; GFR fluctuated by more than 30 % within the 3 months prior to enrollment; hyperkalemia (serum potassium level higher than the upper reference interval limit); history of allergy to any component of the interventions; pregnant or lactating; enrolled in another clinical trial.

### Randomization

Eligible participants will be assigned to each group using blocked randomization, stratified by the participating centers, with a 1:1 allocation ratio using a confidential block size.

Randomization will be performed by the Key Unit of Methodology in Clinical Research (KUMCR) of the Guangdong Provincial Hospital of Chinese Medicine. A computer-generated randomization list created from PROC PLAN in SAS 9.2 (SAS Institute, Cary, NC, USA) will be used. Randomization instructions and blinding codes will be delivered to each participating site via the Interactive Web Response System for Chinese Medicine Trials (IWRS-CMT), a validated web-based randomization system. Each patient will receive a treatment blinding code and all processes will be recorded and saved.

### Blinding

Patients, investigators, monitoring members, outcome assessors, and statisticians will be blinded to group assignment and intervention. The randomization list and blinding codes will remain confidential, and only the KUMCR staff will have access to the randomization list. Blinding will be ensured using the double-dummy method.

### Intervention

Enrollment will be followed by a 3-week run-in period, and then patients will receive BYF plus losartan-matched placebo (CM group) or losartan plus BYF-matched placebo (losartan group) for one year. Patients with unstable BP within the six weeks prior to enrollment that are taking ACEi/ARBs, will be administered other types of antihypertensive agents to reduce BP below 140/90 mmHg.

All Chinese herbs will be obtained from Guangdong Kangmei Pharmaceutical Co. (Guangzhou, Guangdong, China). All herbs will be authenticated by macroscopic and microscopic examination of cross sections, chemical tests and chromatographic analysis. To ensure these herbs are safe for human consumption the agricultural residue screening test for heavy metals, pesticides, and aflatoxins will be performed.

The BYF herbs will be extracted with hot water, then concentrated, spray-dried, and packed in sealed opaque sachets. The entire manufacturing process will comply with Chinese GMP. Sandoz Corp. Ltd. (Zhongshan city, Guangdong, China) will produce the losartan tablet placebos with an identical appearance, smell and taste, packed in exactly the same way.

In the BYF group, patients will be instructed to dissolve a BYF sachet in 150 ml of boiled water and to take this solution orally three times daily and a losartan-matched placebo daily for 1 year. Patients in the losartan group will be instructed to take 100 mg losartan orally once daily and also a placebo sachet dissolved in 150 ml of boiled water three times daily for 1 year.

### Concurrent CKD-related management

All participants will also receive conventional CKD management, including dietary therapy, blood pressure control, management of anemia, regulation of fluid and acid–base disorders, etc., without limitation of dialysis or transplant planning according to the Clinical Practice Guideline [17].

During the intervention period, patients will be advised not to take any other ACEi/ARB or other Chinese medicines with a similar function as the BYF or compound α-ketoacid tablets, and if they do so these patients will be excluded.

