### Statistical analyses

An independent team of data managers and statisticians from KUMCR, will be responsible for the data management and statistical analysis of this study. The statisticians will be blinded to the randomized allocation of groups. PAWS 18.0 (IBM SPSS Inc., Armonk, New York, USA) and SAS 9.2 (SAS Institute Inc., Cary, USA) statistical software packages will be used to analyze the data.

Prior to analyses, the statistical analysis plan will be written, updated and confirmed after blind data review. The full analysis population is defined as patients randomized to receive at least one treatment dose, with baseline and at least one post-baseline efficacy assessment. The per-protocol population is defined as patients who complete the course of the study without a major protocol violation. The primary outcome analysis is based on full analysis population, intention-to-treat principle and the per protocol population. An intention-to-treat analysis will be applied using the imputation method for missing data. The linear trend at point method will be used to replace missing values. The existing series will be regressed on an index variable scaled 1 to n, and the missing values will be replaced with their predicted values. If the predicted values cannot be computed, the last observation carried forward (LOCF) method will be used for this variable. For analysis of endpoint events, a mixed effect model will also be employed, adjusting for co-variables including baseline characteristics. After reporting descriptive statistics of baseline characteristics for each group, an effectiveness analysis will compare the BYF and losartan groups, and a superiority test, with a 95 % confidence interval for eGFR, will be performed to investigate the clinical difference associated with BYF.

The eGFR will be analyzed using a mixed effect GLM with terms for treatment, time point, center, and some baseline characteristics as co-variables based on the concept of repeated measure analysis or adjusted nominal significance level. The Mann–Whitney U-test will be used to analyze ordinal categorical variables. An analysis of variance (ANOVA) will be used for numerical variables, and a Chi-square test or Fisher exact test will be used for categorical variables.

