### Termination and withdrawal

Patients failing to complete the clinical observation will be classified as case dropouts. Investigators will contact these patients and attempt to record the reason for dropping out and the last time they took the studied medicine. Participants will be withdrawal from the study in any of the following situations: 1) commencing permanent renal replacement therapy (dialysis >30 days or kidney transplantation); 2) severe infection, hyperkalemia (K^+^ > 6.5 mmol/L), acidosis (TCO_2_ < 13 mmol/L), or heart failure not curable by medication, deterioration of kidney function that demands dialysis, massive hemorrhage of the gastrointestinal tract, serious arrhythmia dependent on anti-arrhythmic drugs, or uremic encephalopathy; 3) severe primary disease such as an active-stage malignant tumor, decompensating liver cirrhosis, or hematopoietic system disease; 4) urinary tract obstruction that requires surgical treatment; 5) death; 6) withdrawal of consent; 7) transfer to a renal unit which is not an active study site.

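### Patients who take a prohibited drug after randomisation are to be excluded, without saying from what; read plainly, this conflicts with the intention-to-treat analysis and is absent from the withdrawal list

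*Protocol article*

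**What the plan says.** Four parts of the protocol article bear on this.

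- **Concurrent CKD-related management.** The restriction opens: "During the intervention period, patients will be advised not to take any other ACEi/ARB or other Chinese medicines with a similar function". The sentence goes on to cover α-ketoacid as well, and it closes with the consequence for anyone who does not comply: "and if they do so these patients will be excluded". The rule applies after randomised treatment has begun. The sentence does not name what the patient is excluded from.
- **Statistical analyses.** Membership of the full analysis population depends on a dose taken, a baseline value and some later efficacy value; no medication criterion appears. For the second population the wording is: "The per-protocol population is defined as patients who complete the course of the study without a major protocol violation". As to where the primary result is taken from, the section states: "The primary outcome analysis is based on full analysis population, intention-to-treat principle and the per protocol population". Missing values are filled by a linear trend, or by LOCF where the trend cannot be computed.
- **Termination and withdrawal.** The list is introduced by "Participants will be withdrawal from the study in any of the following situations" and gives seven reasons. Use of a prohibited drug is not one of them.
- **Intervention.** The arms are described thus: "patients will receive BYF plus losartan-matched placebo (CM group) or losartan plus BYF-matched placebo (losartan group) for one year". Only the control arm therefore receives an ARB as study drug.

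**The concern.** A rule that removes patients for something that happens after randomisation breaks the comparison that randomisation set up, unless the removals are unrelated to arm and prognosis.

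Here there is a plausible link to arm. The Background section notes that ACEi/ARBs are recommended to lower blood pressure and proteinuria. One arm has an ARB and the other does not. All patients receive blood pressure control, and proteinuria is measured every three months. The findings that prompt a prescriber to add an ACEi/ARB could therefore be more common in the BYF arm. If those patients are also the ones losing eGFR faster, removing them would make that arm look better on the primary outcome.

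A second route is less visible. If exclusion means that follow-up stops while the patient stays in the full analysis population, later eGFR values are never measured and are replaced by extrapolated or carried-forward ones. Sixteen centres could apply the sentence differently, and uncollected values cannot be recovered afterwards.

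**Working it through.** **1. What the sentence could mean**

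| Meaning of excluded | Agrees with the full analysis definition? | Agrees with the withdrawal list? | Effect on the primary comparison |
|---|---|---|---|
| Removed from the trial and the analysis | No: there is no medication criterion | No: not among the seven reasons | Randomised patients lost |
| Follow-up stops, patient kept in the full analysis population | Yes | No | Later eGFR imputed, not observed |
| Removed from the per-protocol set only | Yes | Yes | Full analysis result unaffected |

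Only the third reading fits all the sections, and nothing in the article selects it. The article elsewhere uses exclusion for eligibility, that is, for who may be in the trial. This makes the first reading the plain one.

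**2. The plan's own sample size**

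Inputs from Sample size calculation: declines of 4.5 (SD 4.2) and 6.8 ml/min/1.73 m² per year, margin 1, one-sided 2.5%, power 90%. The distance is (6.8 − 4.5) − 1 = 1.3.

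- Normal approximation: n = 2 × (1.960 + 1.282)² × 4.2² / 1.3² = 219.4, so 220 per group.
- Noncentral t: power 0.8996 at 220 and 0.9009 at 221, so 221 per group.
- Loss of 20%: 221 / 0.8 = 276.25, so 277 per group and 554 in total.

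The stated figures reproduce. They contain no separate allowance for medication exclusions. Keeping these patients in the analysis leaves the sample size unchanged.

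**3. Power if they are removed on top of the 20% loss**

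The shares are assumed. Evaluable n per arm = 277 × 0.8 × (1 − share), normal approximation:

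- 5%: about 210, power 88.8%
- 10%: about 199, power 87.1%
- 15%: about 188, power 85.2%
- 20%: about 177, power 83.0%

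**4. Size of a possible bias**

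Every input here is assumed, because the article gives no rates. If a share p of an arm is removed and those patients decline g more than their whole-arm mean, the retained mean improves by p/(1 − p) × g. The net bias is the BYF shift minus the losartan shift.

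| Removed, BYF vs losartan | g | BYF shift | Losartan shift | Net bias |
|---|---|---|---|---|
| 5% vs 5% | 3.5 | 0.184 | 0.184 | 0 |
| 10% vs 3% | 3.5 | 0.389 | 0.108 | +0.28 |
| 15% vs 5% | 3.5 | 0.618 | 0.184 | +0.43 |
| 10% vs 3% | 6 | 0.667 | 0.186 | +0.48 |
| 3% vs 10% | 3.5 | 0.108 | 0.389 | −0.28 |

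Positive values favour BYF. The last row shows that the sign follows the assumed imbalance.

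**5. Effect on the test**

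With 221 per arm before exclusion, SD 4.2 and no true difference:

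- Test against zero difference: biases of 0.28, 0.43 and 0.48 raise the one-sided error from 2.5% to about 10%, 18% and 21%.
- Test against the margin of 1, which is what reproduces 221: SE = 4.2 × √(2/221) = 0.40, so the estimate must exceed 1 + 1.96 × 0.40 ≈ 1.78. With a bias of 0.48 the chance of that is about 0.0006.

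Against the margin, inflation of the first kind arises only when the true difference is already close to 1.

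**The case against.** The strongest reply is that there is no contradiction. The full analysis population has no medication criterion, the per-protocol population excludes major violators, and absence from the withdrawal list fits the view that a prohibited drug is not a reason to leave the study. On that reading all three sections agree. This is a fair reading and may be what was meant. It does not remove the point, because the sentence is an unqualified instruction to sites and nothing ties it to the per-protocol set.

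The second reply is that the trial is double blind and double dummy, so prescribers do not know who lacks an ARB, and all patients are advised against adding one. Two of the three triggers, similar herbs and α-ketoacid, have no evident link to arm. This stands in part. Blinding conceals the allocation but not the blood pressure or proteinuria that prompts prescribing. An imbalance is therefore possible but not documented.

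Three stronger readings are tempting and should not be drawn:

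- **That the rule will produce a false superiority claim for BYF.** The rates and prognosis are assumed, the direction is uncertain, and a bias of this size would hardly do so against the 1 ml/min margin.
- **That the full analysis population loses everyone without a month-3 eGFR.** It asks for patients "with baseline and at least one post-baseline efficacy assessment", not specifically an eGFR. Serum creatinine is a listed secondary outcome measured at months 1 and 2.
- **That three co-equal analysis sets are named.** The text names two populations and a principle. Ranking them is commonly left to the statistical analysis plan, which is not shown, so the lack of a ranking is not a separate fault.

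**Conclusion.** The point holds as an unresolved inconsistency with a potential for bias, not as a demonstrated removal of patients from the intention-to-treat analysis. The sentence is an affirmative post-randomisation rule. Followed as plainly read, it would drop randomised patients or end their eGFR follow-up, contrary to the stated intention-to-treat basis and outside the withdrawal list.

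The possible bias is about 0.3 to 0.5 ml/min/1.73 m² in the illustrations that favour BYF. This rests wholly on assumed removal of 10% vs 3% or 15% vs 5%, and on removed patients declining 3.5 to 6 more than their arm mean. It is zero with equal shares and equal prognosis, and it reverses if the imbalance reverses. The stated 221 and 277 per group are not affected.

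**What to change.** Reconcile Concurrent CKD-related management, Statistical analyses, and Termination and withdrawal, so that they say the following:

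- Patients who take one of these drugs stay in follow-up and in the full analysis (intention-to-treat) population, with all their observed eGFR values used.
- The drug and its start and stop dates are recorded, and use is reported by arm.
- These patients are removed from the per-protocol set only.
- The full analysis population is the deciding analysis, and per-protocol is supportive.

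Whether study treatment continues in these patients is a clinical matter and is not addressed here.

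The cost is wording in the protocol and the analysis plan and one case report form field. Keeping these patients may slightly dilute the estimated effect through crossover.

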### Outcome measurements

#### Primary outcome

The primary outcome is the change in eGFR over 12 months. Decline of eGFR has been widely applied as primary outcome in several trials, such as the Hypertension (AASK) [20], MDRD Study [21] and the Ramipril in Non-diabetic Renal Failure Study (REIN) [22]. The eGFR will be calculated by the CKD-EPI (Chronic Kidney Disease Epidemiology Collaboration) formula [23], and evaluated at baseline, and after 3, 6, 9 and 12 months of the follow-up period.

